## Study Plan

**1. Study Title :** The Clinical Efficacy of Hip Protection Orthosis for The Protection of Hip Dislocation in Patients with Severe Cerebral Palsy, Single Blinded, Randomized-control trial, Multicenter Clinical Trial

**6. Expected study period**

2 years after the date of IRB approval

**7. Study target disease**

Children with severe cerebral palsy (GMFCS level IV, V)

**8. Background and purpose of the study**

**1) Background**

**(5) cerebral palsy**

Cerebral palsy is a disease that cause abnormal posture and movement due to damage to the immature brain and is one of the most serious disorders occurring in children. Brain damage during pregnancy or before and after birth is common, but in most case, various causes are combined, or the cause is unknown. Brain damage is permanent but non-progressive, and movement disorders in children with cerebral palsy vary depending on the location and extent of brain damage. Cerebral palsy is often classified into spastic type, involuntary movement type, ataxia type, hypotonic type, and mixed type, of which the spastic type accounts for about 70-80%. The frequency of cerebral palsy around the age of 12 years of age reaches 2 to 5 per 1,000 population, and the incidence rate is on a constant or slightly increasing trend.

**(6) Hip dislocation problem in children with cerebral palsy**

Hip dislocation in children with cerebral palsy is caused by excessive stiffness of the muscles around the lower extremities, and the femur falls out posteriorly and outward. The timing of dislocation is very diverse, and it can occur even at an early age of 2-3 years. In particular, the frequency of occurrence increases as standing or walking is delayed or lying down time increases.

Because cerebral palsy is a clinically defined complex syndrome, not a pathological mechanism, the incidence of subluxation and dislocation varies widely depending on the authors, ranging from 3 to 59%, but the frequency of hip subluxation and complete dislocation is cerebral palsy. It is the second most common musculoskeletal complication after equinus deformity in paralyzed children.

In the case of subluxation and complete dislocation, surgical treatment to correct the musculoskeletal is often required, and continuous physical therapy is required even after surgery.

Among children with cerebral palsy, the risk of dislocation increases by 3.9% for GMFCS IV and 9.5% for GMFCS V each year, dislocation examination through X-ray every 6 months is suggested as a guideline.

These hip joint problems adversely affect the walking ability of the patient because walking ability plays an important role in quality of life in the future, research on therapeutic measures to reduce the risk of hip dislocation is needed.

#### **(7) Conservative treatment in children with cerebral palsy**

There is currently no confirmed conservative treatment method to prevent hip dislocation in children with cerebral palsy.

#### **(8) radiological evaluation**

Hip subluxation and dislocation can be evaluated by plain X-ray imaging[Fig 2]. Migration index, which measures the proportion of the femoral head not covered by the hip acetabulum, is widely used.

[figure not shown]

**Figure 2 . Hip migration index**

### 3) Hypothesis and purpose

Hip dislocation occurs more frequently in children with cerebral palsy has not been clearly elucidated, it is expected that the force from strong contraction generated when the adductors are stiff will act in the direction of pulling out the femoral head, increasing the risk of hip dislocation in children with cerebral palsy do. In addition, if the feet are crossed while lying down(scissoring), the risk of subluxation is rather reduced, and when the feet are in contact with each other, the principle of type 1 lever and the principle of length tension relationship work, and it is thought that the abduction torque of the hip joint will increase. At this time, the joint capsule surrounding the hip joint is stretched and ruptured, resulting in dislocation of the hip joint.

This researcher intends to develop a wearable auxiliary medical device to protect the joint capsule of the hip joint that surrounds the hip joint and apply it to prevent dislocation.

The hypothesis of this study is that the hip joint protection wearable auxiliary medical device has the effect of protecting the joint capsule and is expected to reduce dislocation.

To verify the above hypothesis, the purpose of this study is to prove the prevention of hip dislocation by applying this medical device to the study subjects.

hip subluxation and dislocation not only require surgical treatment and long-term rehabilitation, but also adversely affect the child's walking and standing, the results of this study and subsequent clinical trials are expected to improve the quality of life of children with cerebral palsy. are expected to contribute.

## 9. Medical devices for clinical trials

<1st prototype>

[figure not shown][figure not shown][figure not shown][figure not shown]

<2nd prototype>

[figure not shown][figure not shown]

<3rd prototype>

[figure not shown][figure not shown]

<4th prototype>

[figure not shown]

## **10. Selection criteria, exclusion criteria, target number of subjects and calculation basis**

### **1) Inclusion criteria**

- Over 1 year of age and under 10 years of age
- Those with GMFCS level IV or V among children with severe cerebral palsy
- Those who have had quadriplegia or paraplegia for more than 6 months
- hip subluxation /dislocation in children with spastic cerebral palsy occurred before the age of 1 year, so we studied 68 children aged 1 to 10 years set.

### **2) Exclusion criteria**

- If you do not consent to the study
- Those who are judged to be difficult to participate in under the judgment of the principal investigator
- If you have had hip joint surgery or plan to have surgery during clinical trial

### **4) Target number of subjects and calculation basis**

- GMFCS IV and V patients were combined before wearing auxiliary equipment, MI progression / year was measured to be  $7.83 \pm 8.73\%$  (set as a control group) (APMR 2019, IS [name], JS [name], etc.) when data.)
- In this study, the MI of the experimental group was set to  $1.566 \pm 8.73\%$ , assuming that the MI decreased by 80% when wearable auxiliary medical devices were worn.
- When the number of study subjects calculation program (PASS 15.0) was used with Level of significance = 5%, Power = 80%, and Type of test = two-sided, the total sample size was calculated as 32 patients per group and 64 patients in total, and 5% of Considering the dropout rate, a total of 68 experimental and control groups will be recruited.

## **11. Study Subject Recruitment Plan**

Patients with severe cerebral palsy who are undergoing treatment during the study participation period or children who have decided to participate in the study after reading the recruitment notice.

## 12. Specific research methods

Patients diagnosed with severe cerebral palsy were included in the study.

Assignment to experimental group and control group if consent to the study

Subject's body measurements were performed to measure the size of the hip joint wearable medical device.

Radiologic and clinical evaluation were performed to evaluate hip dislocation.

The experimental group manufactured and applied hip-joint wearable medical devices, continue existing rehabilitation treatment.

The control group continued the existing rehabilitation treatment.

6 months and 1-year, clinical evaluation and radiological evaluation were performed to determine the effectiveness.

### 11) Control group setting and randomization method

Experimental group and the control group, a block randomization method is adopted.

Randomization was performed using Microsoft Excel program. A total of 68 study subjects (34 in the experimental group, 34 in the control group) were randomly assigned to a block with a block size of 4 and an allocation ratio of 1:1. In addition, in order to stratify GMFCS IV and V, 68 GMFCS IV and V are assigned respectively.

In the header of cells C4, D4, E4, and F4 of the Excel spreadsheet, enter Sequence, Random number, Block, and Group, respectively. ① Enter the numbers from 1 to 68 in cell C, which is the Sequence column, in order, and ② set the seed (GMFCS IV: 11074, GMFCS V: 11075) using the random number generation function of the data analysis tool for reproducibility in D of the Random number column. to assign a random function. ③ In Block column E, repeat the numbers from 1 to 17 in order. ④ In the Group column, input the experimental group and the control group by 34 consecutively. Then, drag from C4 to F4 to select it, and select Home -> Sort & Filter -> Filter. When a scroll bar appears in each cell, select ascending sort by clicking the scroll bar of E4, and then click the scroll bar of E4 to sort in ascending order to complete the randomization table (Kang, 2017).

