### 1.3 Randomization and Enrollment

In order to prevent an imbalance in the number of study subjects between the experimental group and the control group, a block randomization method is adopted. Randomization was performed using Microsoft Excel program. 24 GMFCS IV and 18 GMFCS V subjects were randomly assigned to two groups with a block size of 4 and an allocation ratio of 1:1. In the header of cells A1, B1, C1, and D1 of the Excel spreadsheet, enter Sequence, Random number, Block, and Group, respectively. ① Enter the numbers from 1 to 24 and 1 to 18 in cell A, which is the Sequence column, in order, and ② enter the function = Rand() in B of the Random number column to assign a random function. ③ In block column C, repeat the numbers 1 to 6 and 1 to 4 in order. At this time, the numbers 1 to 4 or 6 are repeated 4 times, which means that 24 and 18 study subjects were assigned a block size of 4. ④ In the Group column, input the experimental group and the control group, respectively, followed by 12 and 9 people. Then, drag from B1

to D1 to select it, and select Home -> Sort & Filter -> Filter. When there is a scroll bar in each cell, click the scroll bar in C1 to select ascending sort, and then click the scroll bar in C1 to sort in ascending order to complete the randomization table (Kang, 2017). A random number table is created, and a new random function is generated at the start of the study. At this time, the random number on the sheet may change and the assignment may be changed, so copy or capture the value and keep it.

Enrollment : competitive enrollment

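### As written, the list-generation steps sort twice on Block and never on Random number, so they produce a fixed sequence; correct the text and check the archived lists

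*Combined protocol and SAP*

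**What the plan says.** Protocol v13.0, section 12, item 11) describes block randomisation in Excel "with a block size of 4 and an allocation ratio of 1:1". The steps are:

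- Columns: "In the header of cells C4, D4, E4, and F4 of the Excel spreadsheet, enter Sequence, Random number, Block, and Group, respectively". D is therefore Random number and E is Block.
- Lists: "in order to stratify GMFCS IV and V, 68 GMFCS IV and V are assigned respectively", which I read as one 68-row list per GMFCS level.
- Random numbers: "set the seed (GMFCS IV: 11074, GMFCS V: 11075) using the random number generation function of the data analysis tool", entered in column D.
- Blocks: "In Block column E, repeat the numbers from 1 to 17 in order".
- Groups: "In the Group column, input the experimental group and the control group by 34 consecutively".
- Sorting, over a selection running from C4 to F4: "select ascending sort by clicking the scroll bar of E4, and then click the scroll bar of E4 to sort in ascending order". This completes the table.

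Item 12) of the same section then has the coordinating institution's randomisation officer issue numbers in order as each institution enrols.

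SAP v13.0, section 1.3 uses a different layout (A Sequence, B Random number, C Block, D Group) and still describes lists of 24 GMFCS IV and 18 GMFCS V subjects. Its sort instruction is "click the scroll bar in C1 to select ascending sort, and then click the scroll bar in C1 to sort in ascending order". Column B is not sorted.

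**The concern.** Random numbers affect such a list only if the rows are ordered by them at some step. Here both sorts use the block number, and no step sorts on the random number or uses it in any other way. The second sort repeats the first and changes nothing. The typed order of the Group column, all experimental and then all control, therefore carries straight through to the final list.

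The trial's title claims randomisation, and the comparison of change in migration index rests on it. The brace is visible, and protocol item 12) lets the researcher in charge at each institution and the therapist know the allocation. If the next assignment can be foreseen, the decision to enrol a child, or when, can depend on it. An auditor who rebuilt the list from either document would get a deterministic sequence.

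**Working it through.** **Inputs (protocol v13.0, section 12, item 11).** 68 rows per list; Block 1 to 17 cycled; Group 34 experimental (E) then 34 control (C); both sorts on Block. Assumption: tied rows keep their existing order.

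**The plan's own figures.** 17 blocks × 4 = 68 rows, and 34 + 34 = 68, so block size and 1:1 ratio are consistent.

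**Protocol list as written.** Block *k* contains rows *k*, *k*+17, *k*+34 and *k*+51, for *k* = 1 to 17. The first two are at most 17 and 34, so both are E. The last two are at least 35 and 52, so both are C. Every block reads EECC and the list is EECC × 17. Running the steps with 1000 seeds (a generic generator, not Excel's) gave one list, this one. The seeds 11074 and 11075 therefore make no difference and the two strata have identical lists.

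**SAP lists as written (section 1.3).**

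- 24 rows, blocks 1 to 6 cycled, 12 E then 12 C: block *k* contains rows *k*, *k*+6, *k*+12, *k*+18, which are E, E, C, C. Result: EECC × 6.
- 18 rows, blocks 1 to 4, 9 E then 9 C: four repeats fill only 4 × 4 = 16 rows, so I assume the cycle continues for rows 17 and 18. Block 1 (rows 1, 5, 9, 13, 17) is EEECC; block 2 (2, 6, 10, 14, 18) is EECCC; blocks 3 and 4 are EECC. Result: EEECCEECCCEECCEECC, fixed but not a repeated EECC.

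**Other readings.** If Block is filled 1,1,1,1,2,2,2,2 and so on, the protocol list is eight blocks of EEEE, one EECC and eight of CCCC: still fixed, and no longer balanced by block. If ties did not keep their order, the order would still not come from the random numbers.

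**Corrected sort.** Sorting on Random number and then Block gave 1000 different lists from 1000 seeds, every block 2:2. Each block has 6 possible orders, so there are 6^17, about 1.7 × 10^13, possible lists per stratum. The order of the keys matters: Block first and Random number last gave no list out of 1000 in which every consecutive four was balanced.

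**Sort range.** The protocol's selection includes Sequence, so each typed number travels with its typed group. After the Block sort, Sequence reads 1, 18, 35, 52, 2 and so on. If allocation numbers were taken from that column in numerical order, 1 to 34 would be E and 35 to 68 would be C, even with the corrected sort. The SAP's range, B1 to D1, avoids this.

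**Predictability.** In a correct 1:1 block of 4, with block size known and all earlier allocations visible, the best guess is right with probability 1/2, 2/3, 2/3 and 1 at the four positions. The sum is 17/6 = 2.83 of 4, or 71%. Under the fixed list, known pattern and position give 100%.

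**The case against.** The strongest reply is that this is a wording slip. Sorting one column twice serves no purpose, so one key is probably mis-named. The protocol sets seeds for reproducibility, and SAP 1.3 warns that recalculated random numbers could alter the allocation, which makes sense only if allocation depends on them. The text is visibly a rough translation, and recurrence across the protocol and SAP versions fits copied text. All of this stands as to intent. It does not repair the procedure, because neither document states the correct sort anywhere.

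Three stronger readings are tempting and go beyond the documents:

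- **That the trial was not randomised.** The lists used are not in the documents, so this cannot be concluded.
- **That anyone who sees a few allocations can predict the rest.** Protocol item 12) has numbers issued centrally to five competitively recruiting institutions, and item 11) uses two strata. A site need not see the other sites' allocations; it would need the running position as well as the pattern.
- **That predictability rises from 50% to 100%.** The plan specifies blocks of 4, not simple randomisation, so 71% is the fair comparator.

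Item 12) also keeps the principal investigators out of screening and assignment. That safeguard counts, but it is not clean: section 21, item 2) has principal investigators obtaining consent.

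**Conclusion.** The procedure as written is wrong in both current documents. Followed literally, it gives EECC × 17 in both GMFCS strata under the protocol, and EECC × 6 and EEECCEECCCEECCEECC under the SAP, whatever the seed or random numbers. This rests on Block being cycled and on tied rows keeping their order; the alternative block filling is also fixed.

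What follows for the trial is conditional. If the archived lists came from a sort on Random number and then Block, this is a documentation error with no effect on the data. If the written steps were followed, every assignment was predictable to someone who knew the pattern and the stratum's position, selection bias was possible, and the p-values lose their randomisation basis. Only the archived lists can settle which case applies. Separately, the SAP's scheme covers 24 + 18 = 42 children and cannot allocate 68, so correcting its sort key alone would leave an obsolete procedure in place.

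**What to change.** 1. Protocol section 12, item 11): sort ascending on Random number (D4) first and then on Block (E4). Limit the range to Random number, Block and Group (D4 to F4), so that Sequence stays in place.
2. SAP section 1.3: replace the 24/18-subject procedure with the corrected 68-row stratified procedure, so that both documents describe one method.
3. Have the randomisation officer regenerate both lists from seeds 11074 and 11075 with the corrected sort and compare them with the archived lists. If they agree, record that. If the archived lists show the fixed EECC pattern, regenerate any unused slots, disclose how the earlier children were allocated, and qualify the randomisation claim in the report. The protocol describes randomisation in the past tense, so there may be no unused slots; the check and disclosure apply either way.

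The cost is a one-line protocol amendment, one replaced SAP section and an archive check. It needs no extra patients or data collection.

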## **13) Exam drug administration/use, administration/use method, combination therapy, control reason for choosing the drug when using it**

None.

## **14) Observation items, clinical examination items, and observational examination methods**

1. Primary efficacy endpoint: hip dislocation through radiographic evaluation (%)
2. Secondary efficacy endpoints: degree of scoliosis through plain radiograph; Degree of femur anteversion, pain index, Functional changes such as satisfaction with wearable medical devices for hip joint protection, hip and knee joint range of motion, discomfort when caring for a patient, and changes in the patient's overall quality of life were investigated.

## **(4) Hip dislocation test**

Hip subluxation and dislocation can be evaluated by plain X-ray (Hip AP radiography). Migration index, which measures the proportion of the femoral head not covered by the hip acetabulum, is widely used. Measured at initial, 6 months, and 12 months.

[figure not shown]

### Hip migration index

#### (2) Degree of scoliosis

[figure not shown]

To examine the effect of hip fixation on scoliosis, the whole spine AP is taken while sitting in a sitting chair. The degree of scoliosis is measured by the Cobbs angle. Measured at initial , 6 months, and 12 months .

#### (3) Femur anteversion

[figure not shown]

Fig. 1. Anterior-posterior (AP) and lateral (LAT) imaging protocols. In the LAT view, the pelvis is rotated slightly posteriorly to prevent overlap with the femur head.

[figure not shown]

Fig 2. System overview: the anterior-posterior (AP) and lateral (LAT) views are initially pose-estimated using user inputted six points and its 3D correspondences. The image contour is segmented based on the projected contour of the 3D femur. The AP and LAT views are calibrated more accurately using contour correspondences. The shape is optimized so that it projected contour to match the segmented contour. These steps are iteratively performed until convergence.

In the case of Femur anteversion , CT is usually taken, but it has a large amount of radiation exposure. Rather than this , we decided to use a method to measure the anteversion of the femur using simple radiographic examinations such as femur AP and femur lateral x-ray. (K. Youn et al) Measured at the initial stage, 6 months, and 12 months.

#### (4) Joint range of motion

Using a goniometer Measure the range of motion of the hip and knee of the patient

- VI. Hip abduction with hip at 90' flexion
- VII. Hip abduction with hip at 0' flexion
- VIII. Hip adduction with hip at 0 ' flexion
- IX. Hip flexion contracture (Thomas test)
- X. Popliteal angle

#### (5) Questionnaire evaluation

- IV. Pain index (Visual analog scale): In the case of children with cerebral palsy GMFCS IV and V communication is difficult, Assess the patient's hip pain felt by the caregiver.

[figure not shown]

V. Likert scale

- A. Evaluating the satisfaction of wearable medical devices for hip joint protection
- B. Example of this study questionnaire)

Very satisfied - Satisfied - Moderate - Somewhat dissatisfied - Very dissatisfied

VI. Child Health Index of Life with Disabilities (CPCHILD)

- A. As a tool to evaluate the quality of life of patients with severe cerebral palsy It is a tool consisting of 9 items, evaluated by the caregiver. Each item is scored on a scale of 0 to 5, and each item is as follows.
- B. daily activities, postures/movements, comfort and emotions, overall, of life quality, the child's of life vaginal Related of the item Investigate items related to hip contracture among CPCHILDs such as importance
- C. example

**13. From existing treatments and research**

To date, there is no established treatment method to prevent hip joint disease.

There are no medical devices to prevent hip dislocation.

**14. Benefit and Risk of Study Subjects**

**(4) Benefit of study subjects**

Hip dislocation as an examination in clinical trials to be diagnosed with the current state of the hazard Number and provide detailed training on how to manage it.

**(5) Expenses for treatment of study subjects**

There is no additional cost to be paid by the study subject, as the Investigator's cost for clinical evaluation, radiological examination, and orthosis is borne by the Investigator.

**(6) Forecast side effects/risks and countermeasures**

Simple X-ray imaging is an examination method with proven safety. In addition, in the case of children with spastic cerebral palsy, periodic plain X-rays are recommended to evaluate the risk of dislocation (GMFCS IV 4 at 9-month intervals, GMFCS V at 6 month intervals is recommended for surveillance purposes standard of care). Does not increase the risk.

Because the hip dislocation auxiliary medical device is in the form of trousers, special side effects are not predicted, but if a side effect occurs, the treatment cost is paid by the study fund.

